### Hair Loss Determination

Male-pattern and female-pattern hair loss were determined according to the Japanese Dermatological Association’s Guidelines for the diagnosis and treatment of male- and female-pattern hair loss, 2017 version [59]. Male-pattern hair loss was classified by combining the classification method by Norwood [60] and the type II vertex in the classification method by Takashima et al [61], with the type II vertex further divided into 2 groups according to the severity of hair loss. Photographs obtained with a Nikon D5600 from the top of the man’s head and hairline observed from the side were used to classify male-pattern hair loss.

To classify female-pattern hair loss, women’s thinning hair was determined using a total score (0-20 points) of hair appearance (0-10 points), vellus hair rate (0-5 points), hair shedding (0-2 points), and single hair follicular unit (FU; 0-3 points) [62]. A photograph of the midline of the top of the woman’s head was obtained. Using photographs of midline partings, a 5-point scale based on the hair density scale by Sinclair was given a score of 0 to 10 and used to determine thinning of hair in women. An enlarged photograph (20× magnification) of the midline connecting the ears was taken with a digital microscope (KH-7700, Hyrox Co, Ltd), and the numbers of black hairs and gray hairs in a 0.21-cm^2^ area and hair diameter were measured using Image-Pro Plus (ver6.1, Hakuto Co, Ltd). Scores of 0 (vellus hair rate <20%) and 5 (vellus hair rate ≥20%) were used to determine thinning of hair in women. To apply these measurements to determine the initial thinning of hair in women, hair shed during washing was collected with a net (draining net stocking type shallow type for drain holes), and the amount of hair shed (from 10 to 750 hairs) was self-evaluated in 6 stages. The number of hairs lost was divided by the time since the previous hair wash, and the amount of hair shedding was determined. Shedding of 10 to 200 hairs was scored as 0, and hair shedding of ≥400 hairs was scored as 2. The ratio of single hair FUs in the 0.21-cm^2^ area was measured from a 20× magnification image. Single hair FU ratios were scored for women as follows: <25%, score of 0; ≥25% and <50%, score of 1; ≥50% and <75%, score of 2; and ≥75%, score of 3.

### Hand Surface Analysis

Participants were instructed to wash their hands with a commercially available soap [63]. The amount of lactic acid was measured by placing an acrylic cylinder with an inner diameter of 1.5 cm on the hand, adding pure water, and pipetting the mixture. The concentration of l-lactic acid was measured using Lactate Pro 2 (ARKRAY Co Ltd, Inc) with the extracted solution [64]. The measurements were performed twice, and the values were averaged. The skin pH was measured using a multiskin measuring instrument and a skin pH meter (pH 905; Courage+Khazaka Electric GmbH). The surface temperature of the hand was measured using a noncontact thermometer (Shenzhen Hezhizhou Technology Co, Ltd) [65].

### Lipids in the Stratum Corneum and Sebum Analysis

Stratum corneum from the forehead were obtained by stripping with adhesive acrylic film (No. 465 #40, Teraoka Seisakusho). According to a previous report [66], ceramides, free fatty acids, cholesterol, and cholesterol sulfate profiles of the stratum corneum samples were determined using reverse-phase LC-MS.

Face sebum was collected from the forehead using 2 pieces of cigarette paper (Blue double, Rizla Ltd). The sebum was extracted using chloroform or methanol for MS analysis. Sebum MS analysis was performed using flow injection analysis coupled with MS with an ultrahigh performance LC system (Vanquish, Thermo Fisher Scientific) containing a Q-Exactive Focus (Thermo Fisher Scientific) equipped with a heated electrospray source. The Fourier transform MS full-scan mode was used.

### Body Odor Analysis

Participants were instructed not to use products such as deodorants or antiperspirants on their armpits, scalp, and soles of the feet during the night before collection of the body odor sample. Body odor was analyzed using solid-phase microextraction–gas chromatography–MS (SPME-GC-MS). Scalp odor samples were collected by pressing an oil-blotting film (3M Japan) against the parietal scalp ≤4 times at 6 different places and were then stored in a glass vial, immediately frozen, and stored at −80 °C until analysis. Each scalp odor sample was transferred to a 20-mL clear glass vial with a silicone or polytetrafluoroethylene crimp cap for SPME-GC-MS analysis. To collect samples for axillary odor analysis, a cotton pad (Katte Gauze, Ryugu Co, Ltd) infiltrated with 1.2 mL of distilled water was used to swab a 10-cm^2^ area from the armpit at least 10 times for each participant. Foot odor samples were collected from the soles of the feet in the same manner. Each swabbing pad was stored in an aluminum bag with a zipper, immediately frozen, and stored at −80 °C until analysis. Each swabbing pad was centrifuged (6000 revolutions/min, 10 min), and the supernatants were acidified (pH 5.0) with 0.01 N hydrogen chloride and transferred to a 10-mL clear glass vial with a silicone or polytetrafluoroethylene crimp cap for SPME-GC-MS analysis.

### Skin Surface Spectroscopy

#### Advanced Glycation End Product Analysis

The accumulation levels of advanced glycation end products (AGEs) in the skin were measured using an AGE reader (DiagnOptics Technologies) according to the specific protein modifications and fluorescent properties of AGEs [67].

#### Laser Speckle Blood Flowmetry

Facial skin blood flow was measured using laser speckle flowgraphy (a prototype based on LSFG-ANW, Softcare Co, Ltd) [68]. An industrial digital camera (DFK0818UP1300, The Imaging Source GmbH) with a lens (VS-1300VM, VS Technology Corporation) was used to record a series of moving images at a rate of 30 frames/s.

### Cognitive Function Analysis

Cognitive function was assessed using the computer-administered neurocognitive test battery Cognitrax (CNS Vital Signs), for which the validity and reliability have been confirmed [69]. Cognitrax comprises the following battery of tests: a verbal memory test evaluating word learning, word memory, and word recognition, as well as immediate and delayed recall; visual memory test evaluating shape learning ability, shape memory, and shape recognition, as well as immediate and delayed recall; finger-tapping test evaluating motor speed and fine motor control; symbol-digit test evaluating complex information processing accuracy, complex attention, visual perceptual speed, and information processing speed; stroop test evaluating simple reaction time, complex reaction time, stroop reaction time, inhibition and disinhibition, and frontal or executive skills; shifting attention test evaluating executive function, shifting sets (rules, categories, and rapid decision-making), and reaction time; and continuous performance test evaluating the ability to maintain sustained attention, choice reaction time, and impulsivity. A composite neurocognitive index and cognitive domain scores were generated on the basis of the 7 tests.

### Microbiota Analysis

Intestinal microbiota analyses were performed as previously reported [70,71]. Briefly, the participants were instructed to use an FS-0002 tube kit (TechnoSuruga Laboratory Co Ltd) containing guanidine thiocyanate solution to collect fecal samples and store them in a refrigerator (≤4 °C) between visits. Zirconia beads were added to the samples, milled at 5 m/s for 2 minutes using a FastPrep 24 Instrument (MP Biomedicals), and centrifuged for 1 minute at 2350 × g. Bacteria were identified on the basis of the 16S recombinant DNA V3-V4 region. Fragments of the polymerase chain reaction (PCR) mixtures were purified by electrophoresis on 1% agarose gels, followed by PCR Cleanup Filter Plates (Merck Millipore). Illumina paired-end sequencing was performed using the 2 × 300 cycle paired-end method and the MiSeq system (Illumina).

Skin microbiota were collected from the scalp and cheek. To collect scalp microbiota, the hair was parted with a rubber-gloved hand to expose the frontal area of the scalp, and to collect facial skin microbiota, a custom-made sampling template was used to allow for consistent sampling of 4 cm^2^ of the cheek areas. A sterile swab (Nippon Becton Dickinson Company, Ltd) soaked in BBL-prepared saline solution (Becton, Dickinson and Company) was rubbed onto the scalp surface or the designated cheek areas. The head of the swab was cut and placed into a microtube. All samples were frozen at −80 °C until use. The V1-V2 hypervariable region was used as the target for 16S ribosomal RNA (rRNA) gene sequencing. DNA extraction, DNA library preparation, and DNA sequencing were performed by BIKEN Biomics Inc using their standard procedures.

To analyze the saliva microbiota, part of a whole saliva pellet resuspended in sterile water was collected in a 1.5-mL tube and centrifuged for 10 minutes at 15,000 × g at 4 °C. After removing the supernatant, the pellet was stored at −80 °C until the samples were analyzed by Genome Lead Co, Inc. DNA was extracted from each sample using both enzyme treatment and the beads-beating methods (Promega). Then, DNA was extracted from the samples using zirconia beads (EZ-Beads; Promega) and Genfind v2 (Beckman Coulter). The composition of the saliva microbiota was assessed by high-throughput sequencing of the 16S rRNA gene of the V1-V2 region using the Illumina NovaSeq Platform (Illumina). The V1-V2 regions of the 16S rRNA genes from each sample were amplified using primers containing 1 random base sequence at the N position. The 2× KAPA HiFi HotStart ReadyMix (KAPA Biosystems) was used for amplicon PCR and index PCR. Both the PCR products were purified using AMPure XP beads (Beckman Coulter). The amplicon PCR products were purified using AMPure XP beads (Beckman Coulter). NovaSeq sequencing was performed using the NovaSeq 6000 Reagent Kit v1.5 (500 cycles; Illumina) using a 251-bp paired-end sequencing protocol. All 16S rRNA raw sequence data were analyzed using the open-source QIIME2 platform [72], version 2021.2 (qiime2-2021.2).

### SSL‑RNA Analysis

The SSLs collection and SSL-RNA purification were performed as described previously [11]. In brief, an oil-blotting film (3M Japan) was used to wipe the forehead, cheeks, face line, nose, and chin or parietal scalp and stored in a glass vial at −80 °C until analysis. The oil-blotting film was cut into small pieces and homogenized in 1.45 mL of QIAzol (QIAGEN). The SSLs were extracted by placing the supernatant in a tube, adding chloroform, vortexing the mixture for 10 seconds, centrifuging the mixture at 12,000 × g for 15 minutes at 4 °C, and transferring the upper phase to a fresh tube. A RNeasy Mini Kit and QIAcube (QIAGEN) with concomitant DNase I treatment were used to purify the RNA, following the manufacturer’s instructions.

Sequence library preparation was performed using the Ion AmpliSeq Transcriptome Human Gene Expression Kit (Thermo Fisher Scientific), following our previously described modified protocols [11,73,74]. Briefly, the RNA solution was combined with VILO Reaction Mix, SuperScript III enzyme, and T4GP32 (New England Biolabs). The target DNA was amplified using cDNA solution, Ion AmpliSeq HiFi Mix, T4GP32, and the Ion AmpliSeq Transcriptome Human Gene Expression Core Panel with incubation for 20 cycles. We purified the amplified DNA library by binding it to AMPure XP beads (Beckman Coulter), according to the manufacturer’s protocol. A High-Sensitivity D1000 ScreenTape on an Agilent 4200 TapeStation was used to assess the quality of the DNA library. After confirming the quality of the DNA library, the purified library solution was combined with the Ion AmpliSeq HiFi Mix, Ion AmpliSeq Transcriptome Human Gene Expression Core Panel, and VILO Reaction Mix to produce the reaction solution. The adapter sequence was ligated to the library by adding Switch solution, Ion Xpress barcode adapters, and DNA ligase to the reaction solution and then incubating the mixture. The libraries were eluted from the beads using Library Amp Mix (Thermo Fisher Scientific) containing Library Amp Primers. An aliquot of the PCR product was purified using AMPure XP beads, and the supernatant was transferred to fresh PCR tubes. The quality of the sequence library was assessed using the High-Sensitivity D1000 ScreenTape on the Agilent 4200 TapeStation. An Ion Library TaqMan Quantitation Kit (Thermo Fisher Scientific) was used to quantify the library. After loading the DNA library in the Ion Chef System (Thermo Fisher Scientific), the template was prepared and the chip was loaded, and the Ion S5 XL System (Thermo Fisher Scientific) was used to perform the RNA sequencing.

### SSL-Protein Analysis

Proteins for SSL-protein analysis were prepared using S-trap micro columns (ProtiFi), according to the partially modified procedure described in the manufacturer’s protocol. In this study, sodium deoxycholate and sodium lauryl sulfate were used for the protein solubilization solution. Following the removal of SSL-RNA from the upper layer, 2-propanol was added to the residual solution. After centrifuging at 14,000 × g for 5 minutes, the precipitate was dissolved in a protein solubilization solution and applied to an S-trap column. The eluted tryptic digest was concentrated under reduced pressure and desalted using styrene divinylbenzene polymer GL-Tip (GL Sciences) according to the manufacturer’s protocol. The peptide mixtures were subjected to LC-MS/MS. LC separations were performed with a nano-HPLC system Ultimate 3000 (Thermo Fisher Scientific) using an Acclaim PepMap 100 analytical column (Thermo Fisher Scientific). MS detection was performed with a Q-Exactive Plus (Thermo Fisher Scientific) in positive-ion mode and operated in the data-dependent acquisition mode and data-independent acquisition mode. Analysis of the acquired data was performed using Mascot database search (Matrix Science) and DIA-NN software (version 8.1; GitHub) [75].

### SSL-Metabolite Analysis

The SSLs for metabolite analysis were collected by wiping oil-blotting paper around the neck below the face line, and the samples were stored in glass vials at −80 °C until use. To extract metabolites, the oil-blotting film was cut into small pieces and placed in a glass vial with methanol. The supernatant was filtered through a DISMIC-13HP 0.45-μm syringe filter (Advantec) and concentrated under reduced pressure until dry. Each sample was redissolved in 80% (volume/volume) methanol and filtered through a DISMIC-13HP 0.45-μm syringe filter. A portion of the filtrate from each sample was mixed in equal volumes to create a pooled quality control sample.

SSL-metabolite analysis was conducted using an ExionLC system (AB Sciex) coupled to an AB SCIEX X500R electrospray-ionization quadrupole time-of-flight high-resolution MS (AB Sciex). The LC system comprises a 2-channel pump, a degasser, a column oven, an autosampler, and a controller. LC was performed by injecting the sample onto an L-column3 C18 reversed-phase column (Chemicals Evaluation and Research Institute).

We used the sequential window acquisition of all theoretical mass spectra. In total, LC-MS analysis was performed in 10 batches. The quality control dilution series was used to confirm the linearity of the metabolites. Data processing, including automatic peak finding, locally weighted scatterplot smoothing normalization, and identification via spectra matching, was performed using MS-DIAL (version 4.7; downloaded from the PRIMe website) [76]. All automatically detected peaks were checked manually, and the linearity of each metabolite was checked using diluted quality controls, excluding peaks with low linearity (*r*≤0.85).

### Statistical Analysis

#### Data Management

The data of each participant were managed using an electronic database and case record forms. There were 2 levels of data quality control. The first level of quality control was conducted by the investigators while entering the records into the case record form. For the second level, an independent group conducted data monitoring and validation. An electronic database served as a double-entry system to further ensure accurate data input.

#### VHGM Analysis

We will construct a generative model to capture the joint distribution among the aforementioned health care attributes. As the attributes comprise both numerical and categorical values, a model that can handle this type of heterogeneity must be selected. To this end, we will use the heterogeneous incomplete variational autoencoder (HIVAE) [8]. The HIVAE is an extension of a variational autoencoder [77] in which a different likelihood function can be selected depending on the attribute type. For example, we will input the normal distribution for weight and height and the categorical distribution for sex (male, female, and other). Given a set of observed attributes as inputs, we can use the trained model to estimate the parameters of the (conditional) probability distribution of each attribute, including the missing ones. The objective function of HIVAE is called the evidence lower bound, which measures the discrepancy between the training data set and the model. We will separate the entire data set into training and testing sets and train the model to minimize the evidence lower bound to fit the training data set.

We will evaluate the performance of the trained model in terms of 2 perspectives: (1) predictability of missing attributes and (2) representability of the empirical distribution. For the first perspective, we will randomly generate missing patterns on the testing set and measure the prediction accuracy. For the second perspective, we will manually compare the joint distribution of the model and the data on several attribute pairs that would have a strong relationship (eg, age and blood pressure) to ensure that there is no notable discrepancy.

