### Blood Pressure and Arterial Stiffness Measurements

Heart rate, systolic blood pressure, and diastolic blood pressure were measured with the participants in a sitting position using a VS-2500 Vascular Screening System (Fukuda Denshi Co, Ltd). Measurements of the cardio-ankle vascular index and ankle brachial index were obtained while the participants assumed a supine position using the VS-2500 Vascular Screening System with an electrocardiogram, phonocardiogram, and brachial and ankle artery pressures and waveforms [50]. The cardio-ankle vascular index was automatically calculated for the left and right sides, and both values were used for analysis.

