### Oral Glucose Tolerance Test

Other than the participants diagnosed with diabetes or other potentially serious illnesses, all participants underwent an oral glucose tolerance test at visit 2 after fasting overnight. After the fasting blood sample was collected, a 75-gram glucose load was ingested. Blood samples were obtained at 30 minutes and 120 minutes after the glucose load. Glucagon, active glucagon-like peptide-1, total glucose-dependent insulinotropic peptide from plasma, insulin, growth hormone, and insulin-like growth factor 1 from the serum were measured using enzyme-linked immunosorbent assay kits (glucagon: Mercodia; active glucagon-like peptide-1: Immune Biology Laboratories; total glucose-dependent insulinotropic peptide: Merck KGaA; and growth hormone and insulin-like growth factor 1: R&D Systems). Plasma glucose and serum insulin were assessed according to standard procedures at the laboratory at Health Sciences Research Institute, Inc (Kanagawa, Japan).

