## Discussion

### Principal Findings

High-dimensional cross-sectional studies are rarely conducted. We believe that there are several methods to use such data sets. We plan to provide the VHGM that we are developing as a commercial service via an application program interface (API) on the internet. Any application program can send a query to the VHGM, such as *what is the mean and variance of systolic blood pressure of Japanese adults? (marginal probability)*; *what is the probable distribution of blood glucose levels given my age, sex, and lifestyle (excursive, drinking, and smoking habits)? (conditional probability)*; and *what would my estimated cognitive function index be if my age were 10 years older (counterfactual inference)*. We are expecting to discover many innovative health care applications using the VHGM API.

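### The two stated checks of the Virtual Human Generative Model are not matched to the queries it is meant to answer, so reported accuracy may be optimistic for them

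*Protocol article*

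**What the plan says.** Under VHGM Analysis, the article fixes the evaluation as follows.

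- **Split:** "We will separate the entire data set into training and testing sets". The fraction is not given, and it is not said whether this means the study data or the study and commercial data together.
- **Check 1, prediction of missing attributes:** "we will randomly generate missing patterns on the testing set and measure the prediction accuracy". The unit masked (single value or whole panel), the masking rate and the accuracy metric are not stated.
- **Check 2, fidelity of the distribution:** "we will manually compare the joint distribution of the model and the data on several attribute pairs that would have a strong relationship", with age and blood pressure as the example. The aim is "to ensure that there is no notable discrepancy".

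The intended use is under Principal Findings. One example query to the planned commercial service is "what is the probable distribution of blood glucose levels given my age, sex, and lifestyle". The Introduction (Background) says the model will join more than 1 million low-dimensional records to about 1000 high-dimensional ones, and leaves the method of combining them to another publication.

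One panel is missing by design in some people: "Other than the participants diagnosed with diabetes or other potentially serious illnesses, all participants underwent an oral glucose tolerance test at visit 2".

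**The concern.** An accuracy figure is informative for a query only if the test hides what the query hides. In the example query the user knows age, sex and lifestyle, and every assay panel is unknown. In the commercial records, by inference from the Background text, the panels unique to this study are absent as whole blocks.

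Many attributes have near-duplicates. For the arterial stiffness measure, "The cardio-ankle vascular index was automatically calculated for the left and right sides, and both values were used for analysis". Anthropometric Measurements lists body fat as both a percentage and a mass from one device. Cognitive Function Analysis derives a composite index from its own seven tests. If single values are hidden at random, such siblings usually stay visible and the task becomes easier than the one a user sets.

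The pair check has a related weakness: it looks at the relations that the model is most likely to reproduce, by eye and without a numerical criterion. Strengths and Limitations, however, expects previously unknown relationships among thousands of variables.

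At stake is whether the published accuracy describes the service that is offered.

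**Working it through.** The article gives no model accuracy, masking rate or test-set size, so there is no figure to reproduce. The calculations below show direction only; their settings are assumptions.

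**1. Random against query-matched masking.** Assume 200 standardised Gaussian attributes in 20 panels of 10, with correlation w within and b = 0.2 between panels. R² is the exact share of variance explained by the observed attributes.

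- *30% random masking.* About 9 × 0.7 = 6.3 siblings remain visible. From k siblings alone, R² = k·w² / (1 + (k − 1)·w). For k = 6 and w = 0.8: 3.84 / 5.0 = 0.77. For w = 0.6: 2.16 / 4.0 = 0.54. The exact calculation with all observed attributes, averaged over 200 random masks, also gives 0.77 and 0.54.
- *Whole panel masked.* The 19 other panels remain: R² = 19·b² / ((1 + 9w)/10 + 18b). For w = 0.8: 0.76 / 4.42 = 0.17. For w = 0.6: 0.76 / 4.24 = 0.18.
- *Three attributes known, each from a different other panel.* R² = 3·b² / (1 + 2b) = 0.12 / 1.4 = 0.09 for either w.
- *No panel structure (w = b = 0.2).* Random masking leaves about 140 attributes: 140 × 0.04 / (1 + 139 × 0.2) = 5.6 / 28.8 = 0.19. Whole-panel masking leaves 190: 7.6 / 38.8 = 0.20. That gap vanishes. The three-attribute query stays at 0.09, simply because less is known.

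**2. The same comparison with a fitted predictor.** A shrinkage-covariance Gaussian predictor stood in for the HIVAE (800 training and 197 test records, 5 replicates, all assumed).

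| Correlation within / between | Random values masked, 10–80% | Whole panel masked | Only one low-dimensional panel seen |
|---|---|---|---|
| 0.7 / 0.3 | 0.52–0.62 | 0.18 | 0.12 |
| 0.5 / 0.1 | 0.27–0.35 | −0.09 | 0.01 |
| 0.3 / 0.1 | 0.09–0.11 | −0.10 | 0.02 |
| 0.2 / 0.2 | 0.05–0.15 | 0.03 | 0.14 |

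The direction agrees wherever within-panel correlation exceeds between-panel correlation.

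**3. How often independent masking of values hides a full panel.** For 10 attributes the probability is 0.2¹⁰ = 0.0000001 at 20% masking, 0.5¹⁰ = 0.001 at 50% and 0.8¹⁰ = 0.11 at 80%.

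**4. Coverage of the pair check.** Assume 1000 attributes, the low end of thousands: 1000 × 999 / 2 = 499,500 pairs. Ten inspected pairs (assumed) are 0.002% of them.

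**5. Precision from a single split.** An assumed 20% test set gives 0.2 × 997 = 199 participants. For r = 0.30, Fisher's z is 0.310 with half-width 1.96 / √196 = 0.140, so the 95% interval is 0.17 to 0.42. With all 997 scored by cross-validation, the half-width is 1.96 / √994 = 0.062 and the interval about 0.24 to 0.36.

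**6. Glucose tolerance values.** VHGM Analysis says the trained model estimates attributes that were not observed. Participants with diagnosed diabetes or other potentially serious illness have no glucose tolerance values. Hiding and recovering a value requires that it was measured, so no masking scheme, random or by panel, can test this output for them. This needs no simulation.

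**The case against.** The strongest reply is that the article does not fix the unit or rate of masking. Random masking of whole panels would fit the same words and would partly test the intended queries. Such detail often sits in a fuller document, combining the data sources is expressly deferred, and the primary objective is to build the data set. This stands as far as it goes: a reader might infer that the plan certainly overstates accuracy, and the documents do not show that. But the article does name its two checks and commits neither to the use it describes.

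Five other strong readings are tempting and should not be drawn.

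- *That a model with no cross-panel ability would pass.* No pass threshold is stated, and the example pair, age and blood pressure, itself crosses panels.
- *That random masking answers a question nobody asks.* The Background names estimating missing or corrupt values as a use, and random masking tests that.
- *That conditional spread is never examined.* Comparing joint distributions does show spread for the inspected pairs, though informally.
- *That test accuracy would mainly describe the commercial data.* The study supplies 997 / 1,000,997 = 0.1% of combined records, but only if the split covers both sources and one pooled figure is reported. Accuracy is scored on values, not records. Assuming 1000–5000 study attributes and 20–50 commercial ones, the study's share of values is about 2–20%.
- *That the blood glucose query concerns the glucose tolerance test.* Laboratory Analysis lists plasma glucose without excluding people with diabetes; only the tolerance test has that exclusion.

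**Conclusion.** The concern holds in a limited form. The two stated checks are not matched to queries in which few attributes are known and whole panels are absent, and the pair check is informal and confined to pairs expected to be strong. If masking is value by value and panels are internally correlated, reported accuracy is likely to be optimistic for those queries. The measurement sections make some internal correlation very likely; value-by-value masking is an assumption.

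The size cannot be derived from the documents. The contrast of 0.77 with 0.17 and 0.09 belongs to an assumed correlation matrix, and the difference between random and whole-panel masking disappears without panel structure. The glucose tolerance gap is firmer: it follows from the exclusion itself and does not depend on how values are masked.

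This is a worthwhile, inexpensive improvement to the evaluation. It does not show that the model will perform poorly.

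**What to change.** 1. Keep random masking as a supplement. As the main accuracy measure, add (a) masking of each assay panel in full and (b) masking of everything except demographics, lifestyle and routine check-up items. State the unit, rate and metric.
2. Report accuracy per attribute in the study participants, by cross-validation (for example 5- or 10-fold), so that all 997 contribute.
3. Replace the manual comparison with held-out coverage of the conditional intervals (for example 50% and 90%) for each attribute, and with model-minus-data differences in rank correlation over all pairs or a random sample of pairs.
4. Label glucose tolerance output as not validated for people with diagnosed diabetes or the other potentially serious illnesses excluded from the test.

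No new data are needed. The cost is revised analysis wording, more computing and probably a lower reported accuracy. These steps would still not validate the counterfactual age query under Principal Findings, because the data are cross-sectional.

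### The model is to supply variances and conditional distributions, but the only quantitative test described is an unspecified prediction accuracy and the only distributional check is a manual look at a few strongly related pairs, so wrong spread or lack of skill could go undetected elsewhere.

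*Protocol article*

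**What the plan says.** The VHGM Analysis section of the protocol article describes a heterogeneous incomplete variational autoencoder that returns, for each attribute, the parameters of a conditional probability distribution. On the data split it says "We will separate the entire data set into training and testing sets"; no fraction and no number of splits is given. Training uses a likelihood-based criterion: "The objective function of HIVAE is called the evidence lower bound". That criterion is named for training and not as a test-set score.

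Evaluation has two perspectives:

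- Predictability of missing attributes: the plan is to generate missing patterns at random "on the testing set and measure the prediction accuracy".
- Representability of the empirical distribution: "we will manually compare the joint distribution of the model and the data on several attribute pairs that would have a strong relationship", with age and blood pressure as the example. The stated aim is "to ensure that there is no notable discrepancy".

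The Principal Findings section gives examples of what the service should answer. One is a marginal query, "what is the mean and variance of systolic blood pressure of Japanese adults". Another is a conditional query with several inputs, "what is the probable distribution of blood glucose levels given my age, sex, and lifestyle".

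**The concern.** What is delivered to users is spread and shape as well as a central value: a variance, or a distribution given several personal characteristics. The checks should therefore show whether the stated spread is right and whether the model knows more than a simple reference does.

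The first check gives a number, but in its ordinary sense prediction accuracy compares a predicted value with the observed one, and the width of the predicted distribution does not enter. It also has no reference, so a high figure for an uncommon category cannot be told apart from always giving the common answer.

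The second check does concern distributions. It is made by eye, has no statistic or limit, and covers only pairs picked for their strong relationship. A comparison of pairs also does not verify a distribution conditional on several inputs at once, which the blood glucose query needs.

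At stake is whether a good reported accuracy could accompany predictive ranges that are clearly too narrow or too wide.

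**Working it through.** The article states no performance figure, threshold or split fraction, so there is no figure of the plan to reproduce. What follows illustrates what each check can and cannot see.

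**Inputs.** From the article: 997 participants enrolled (Results) and thousands of variables (Strengths and Limitations). Assumed: a bivariate normal pair with unit SDs and correlation r = 0.5; a correct conditional mean; a model conditional SD equal to k times the true one; a binary attribute with 5% prevalence; and a test fraction of 10% to 30%.

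**Step 1: spread.** With a correct mean:

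- Root mean squared error = √(1 − r²) = √0.75 = 0.866, for every k.
- Coverage of the nominal 95% range = 2Φ(1.96k) − 1.
- Expected negative log score = ½ ln(2π × 0.75) + ln k + 1/(2k²).
- Marginal SD implied by the model = √(r² + k²(1 − r²)).
- Pair correlation implied by the model = r divided by that marginal SD.

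| k | RMSE | 95% coverage | Neg. log score | Implied correlation | Implied marginal SD |
|---|---|---|---|---|---|
| 0.5 | 0.866 | 67.3% | 2.08 | 0.76 | 0.66 |
| 0.7 | 0.866 | 83.0% | 1.44 | 0.64 | 0.79 |
| 1.0 | 0.866 | 95.0% | 1.28 | 0.50 | 1.00 |
| 1.3 | 0.866 | 98.9% | 1.33 | 0.41 | 1.23 |
| 2.0 | 0.866 | about 100% | 1.59 | 0.28 | 1.80 |

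A simulation of 200,000 draws at k = 0.5, 1 and 2 agreed closely (RMSE 0.864; negative log scores 2.07, 1.27 and 1.59).

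Point error is the same in every row. Coverage and the log score separate the rows. The last two columns show what the manual check could reveal in a pair that is actually inspected: a halved SD moves the correlation from 0.50 to 0.76.

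**Step 2: skill.** If accuracy means the proportion correctly classified, always giving the commoner answer scores 1 − prevalence: 95% at 5% prevalence, 90% at 10% and 80% at 20%. Without a reference, these figures say nothing about the model.

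**Step 3: reach of the manual check.** Even 1,000 variables give 1,000 × 999 / 2 = 499,500 pairs. The article plans to inspect several.

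**Step 4: precision (secondary).** For a predicted-observed correlation near 0, the 95% half-width is tanh(1.96/√(n − 3)). A test set of 100 people (10% of 997) gives ±0.20, and 299 people (30%) gives ±0.11. If all 997 had out-of-fold predictions, it would be about ±0.06. That last value treats predictions from different folds as if they came from one model, so it is approximate.

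**The case against.** The strongest reply is that the plan does look at distributions. The second perspective targets shape, its example pair involves the same kind of attribute as the blood pressure query, and Step 1 shows that gross errors in spread could be seen there. A model with no skill beyond base rates would show correlation 0 in such a pair. This stands. A reader might infer that a model with wrong spread or no skill would pass the plan's evaluation. The article does not support that, because the second check could expose such a model in the inspected pairs and no pass threshold is stated.

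A second reply is that point prediction and a single hold-out split are readings of the text. The article names no metric and does not exclude a distributional score or repeated splits. This also stands. The figures on point accuracy apply only if the ordinary meaning is intended.

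Third, the article is condensed, its primary objective is to obtain the data set, and it leaves the combining of the data sets to a separate publication. Metric and split details may be given elsewhere, and their absence alone is no fault. What remains is that the article chooses its two perspectives and the method for each. As described, neither quantifies spread, calibration or skill over a reference outside the inspected pairs. The separate publication is announced for combining the data sets; evaluation is not mentioned there.

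Fourth, the likelihood-based training objective fits spread. That is true, but a fit to training data does not show calibration on new people.

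Finally, attributes shared with the commercial data set of more than 1 million records need not be limited to small test numbers. Step 4 concerns only the high-dimensional attributes.

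**Conclusion.** The point holds in limited form. The evaluation described does not match the declared outputs: its only quantitative measure is a prediction accuracy with no named metric or reference, and its only distributional check is manual, has no criterion and is confined to several favourable pairs. Wrong predictive spread, or lack of skill beyond base rates, could go undetected for attributes and multi-input conditionals outside those pairs.

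The size is illustrative. With a correct mean and normal errors, an SD at 0.5 or 0.7 of the truth reduces nominal 95% coverage to 67% or 83% without changing point accuracy. These SD ratios are assumptions, and nothing in the article shows that the model will be miscalibrated. The precision loss from a hold-out set is secondary, because the split fraction and the number of splits are not stated. The change is worth making before results are reported, since a better method is available at low cost.

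**What to change.** In the VHGM Analysis section, keep both perspectives and add the following for each attribute, computed on held-out data:

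- a proper score: log score or continuous ranked probability score for numerical attributes, Brier or log score for categorical ones;
- observed coverage of predictive ranges, for example 50% and 95%, overall and by sex and age group;
- skill on the same score relative to a reference model that uses age and sex only.

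Report these alongside the model's distributional outputs. Possible wording: *Predictive performance on held-out data will be summarised for each attribute by a proper scoring rule, by observed coverage of the 50% and 95% predictive ranges overall and by sex and age group, and by skill relative to a model using age and sex only.*

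Cross-validation over the 997 high-dimensional records is an optional gain in precision. With five folds it would need about five model fits in place of one.

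The cost is analysis work. No new data and no burden on participants are involved. Reported performance may look less favourable than a single accuracy figure.
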